# Increasing access to fertility preservation for women with breast cancer: protocol for a stepped-wedge cluster randomized trial in France

**DOI:** 10.1186/s12889-024-17719-3

**Published:** 2024-01-19

**Keywords:** Fertility preservation, Breast cancer, Combined intervention, Information, Practitioners training, Social inequalities in health, Participatory approach

## Abstract

**Background:**

With the increase in the number of long-term survivors, interest is shifting from cancer survival to life and quality of life after cancer. These include consequences of long-term side effects of treatment, such as gonadotoxicity. Fertility preservation is becoming increasingly important in cancer management. International recommendations agree on the need to inform patients prior to treatments about the risk of fertility impairment and refer them to specialized centers to discuss fertility preservation. However, the literature reveals suboptimal access to fertility preservation on an international scale, and particularly in France, making information for patients and oncologists a potential lever for action. Our overall goal is to improve access to fertility preservation consultations for women with breast cancer through the development and evaluation of a combined intervention targeting the access and diffusion of information for these patients and brief training for oncologists.

**Methods:**

Firstly, we will improve existing information tools and create brief training content for oncologists using a qualitative, iterative, user-centred and participatory approach (objective 1). We will then use these tools in a combined intervention to conduct a stepped-wedge cluster randomized trial (objective 2) including 750 women aged 18 to 40 newly treated with chemotherapy for breast cancer at one of the 6 participating centers. As the primary outcome of the trial will be the access to fertility preservation counselling before and after using the combined intervention (brochures and brief training for oncologists), we will compare the rate of fertility preservation consultations between the usual care and intervention phases using linear regression models. Finally, we will analyse our approach using a context-sensitive implementation analysis and provide key elements for transferability to other contexts in France (objective 3).

**Discussion:**

We expect to observe an increase in access to fertility preservation consultations as a result of the combined intervention. Particular attention will be paid to the effect of this intervention on socially disadvantaged women, who are known to be at greater risk of inappropriate treatment. The user-centred design principles and participatory approaches used to optimize the acceptability, usability and feasibility of the combined intervention will likely enhance its impact, diffusion and sustainability.

**Trial registration:**

Registry: ClinicalTrials.gov. Trial registration number: NCT05989776. Date of registration: 7^th^ September 2023. URL: https://classic.clinicaltrials.gov/ct2/show/NCT05989776.

**Protocol version:**

Manuscript based on study protocol version 2.0, 21st may 2023.

**Supplementary Information:**

The online version contains supplementary material available at 10.1186/s12889-024-17719-3.

## Background

With advances in cancer treatments and the increase in long-term survivors, concerns are shifting from survival to quality of life after cancer and long-term side effects of treatments [1, 2]. Treatments combining surgery, radiotherapy, and chemotherapy are likely to alter reproductive function and quality of life after cancer [3, 4]. Access to fertility preservation is an essential element of quality of life for patients and their families after their recovery [5]. It is therefore becoming an increasingly important part of cancer management.

In many countries, recommendations include informing patients of the risks of infertility associated with cancer treatment, and referring them as soon as possible after diagnosis to a specialized center for fertility preservation consultations [6–8]. In France, since 2004, there is a legal obligation to offer fertility preservation to any woman or man exposed to a treatment likely to impair their reproductive function [9]. In 2018, a study based on National French data estimated that between 17,200 (10,400 men and 6,800 women) and 40,000 (30,000 men and 10,000 women) patients of childbearing age were eligible for fertility preservation consultations and associated fertility treatments [10]. Focusing our attention on women, fertility preservation data provided by the French National Biomedicine Agency estimated that about 750 ovarian tissue self-preservations were carried out in 2013 [11], rising to 3,500 in 2018 [12]. These figures remain very far away from the expected number of individuals concerned, highlighting the need to drastically improve information and access to fertility preservation counselling.

In Europe, a Dutch retrospective study conducted at the Radboud University Medical Center found that only 9.8% of all eligible patients under the age of 40 and seen at a university hospital in 2011 were referred for fertility preservation counselling. In addition, this study found that referral to counselling was hampered by a lack of information about the services offered by fertility preservation centers, and by a lack of collaboration among healthcare providers [13]. In Denmark, a study conducted in 2023 among young women with cancer and informed of the risks to their fertility showed that their doctors’ choice of treatment was not in favour of preserving their fertility, as survival was more important [14]. In France, a lower rate of self-reported discussion of infertility risk (46%) was reported by the 102 of 1161 oncologists who responded to a national survey between 2012 and 2013. Moreover, only 22% of oncologists reported referring the patient to a fertility center before starting treatments [15]. More recently, the FEERIC study (FErtility, prEgnancy, contRaceptIon after breast Cancer in France) showed that around 46% of survey respondents were offered specialized oncofertility counselling [16].These results are all the more worrying considering that 80% of female respondents had a high level of education, with university degrees and therefore a high level of literacy.

French regional studies carried out in Occitanie (a region in the south-west France with a population of 6 million) have shown that only 23% of women under 40 treated with chemotherapy for breast cancer received an oncofertility consultation and 8.7% received fertility preservation between 2012 et 2017. Only 44% of oncologists were confident that ovarian stimulation treatment could be used, and 29% overestimated the time required for fertility preservation [17]. Information and access to an oncofertility consultation were influenced by the type of care structure, the woman’s age, her parity at the time of diagnosis, and the metastatic status of the cancer [18]. Furthermore, another regional study showed that if all women were informed of the risks of hypo fertility related to chemotherapy, then gamete preservation could be increased by 15.35% in women aged < 30 and 22.88% in women aged 30 to 35 [19].

These data suggest that strategies are needed in France to improve access to fertility preservation. A number of teams from different countries have highlighted the importance of implementing decision-support tools to improve access to fertility preservation, particularly for younger women with cancer, but also for healthcare professionals [20]. In some French regions, information tools have been created for patients and healthcare professionals, but to our knowledge, neither these tools nor any other user-centred strategy to improve access to fertility preservation have been evaluated. Randomized trials are currently underway to evaluate the impact of these tools on the recourse to fertility preservation [21–24]. Some preliminary results are showing the importance of information for patients about the different fertility preservation options available [23, 24].

Our overall aim was to improve access to fertility preservation and related consultations for women with breast cancer through the development and evaluation of a combined intervention targeting the access and diffusion of information for these patients and brief training for oncologists.

## Methods

The trial protocol follows the SPIRIT guidelines (see Additional File 1) and the flow diagram is presented in Fig. 1:

**Fig. 1 Fig1:**
[figure not shown]
Flow diagram

### Objective 1

To improve existing information tools and access about fertility preservation for patients with breast cancer and raise awareness about fertility preservation (brief training) for healthcare professionals.

#### Hypothesis 1.1

Improving access to fertility preservation services depends largely on the availability and quality of information on the risk of gonadotoxicity associated with certain cancer treatments and information on fertility preservation consultations, as well as available treatment options.

#### Hypothesis 1.2

A participatory approach, involving patients and professionals, will highlight current gaps in the information available to each stakeholder.

### Objective 2

To evaluate the impact of a combined intervention for patients and health professionals on access to fertility preservation using a stepped-wedge cluster randomized trial.

#### Hypothesis 2.1

A significant improvement in access to fertility preservation consultation (primary outcome measure) is expected after the intervention.

### Objective 3

To conduct a context-sensitive implementation analysis to identify key elements for transferability and implementation in other contexts.

#### Hypothesis 3.1

The FIC (key Function, Implementation, Context) model [25, 26] used in this approach will highlight the transferable theoretical elements that underline the activities implemented in a particular context, while taking into account the new context in which they can be implemented.

### Intervention

The planned intervention for our trial is combined, targeting both health professionals and eligible patients, it includes brochures and awareness training for healthcare professionals on fertility preservation (time required, various techniques available, prerequisites…) developed in collaboration with Regional Cancer Networks (RCNs) in Pays de la Loire et Occitanie. RCNs have been leading working groups made of oncologists, gynaecologists and biologists specialized in fertility preservation, in 2018 and 2019 respectively. The aims of these working groups were to create brochures for patients and health professionals, to facilitate interprofessional exchanges and to transmit information about fertility preservation for all cancer patients (children, men, women…). The effectiveness of the brochures created so far has not been tested, and there is no hindsight or feedback from patients or healthcare professionals regarding their acceptability, usability and usefulness.

These brochures will be adapted and improved to account for limited health literacy (HL) [27] using a participatory approach with focus groups and semi-structured interviews. Semi-structured interview guides (and focus group moderation guides) will be developed using cognitive debriefing and think-aloud techniques. We will use Morville’s user experience framework to develop all guides and questionnaires. Team members have used these techniques successfully before [28, 29]. Participants will be recruited through the RCNs. The focus groups will include patient partners, who have followed a specific training course in participatory research, and/or patients who have been affected by cancer in the past, and healthcare professionals involved in the fertility preservation process, who are members of the oncofertility working group from both participating regions. Focus groups (and interview) participants will be asked to primarily focus on reviewing the existing brochures in Occitanie and Pays de la Loire and suggesting improvements to increase acceptability, usability and adapt content for patients with limited HL. Healthcare professionals will also suggest content and format for the health professionals’ awareness-raising training. The transcripts of these focus groups and semi-structured interviews will be analysed using Nvivo 14 software [30]. We will then use the transcribed data from the focus-groups and interview to update the brochures and develop awareness-raising training. The acceptability, usability and accessibility of these updated tools will then be tested in a second round of semi-structured interviews with other patient partners and healthcare professionals.

Particular attention will be paid to the readability of the brochures. We will follow plain language recommendations [31] to improve the readability of existing brochures and address limited HL. Written contents will be checked using an online readability software (www.scolarius.com). Because this combined intervention has multiple interacting components targeting both eligible patients and healthcare professionals, it is defined as a complex intervention. We will therefore follow the updated Medical Research Council (MRC) framework for evaluating complex interventions [32].

### Trial design

We will conduct a two-arm, multi-site, stepped-wedge cluster randomized trial in two participating French regions over a 30-months period (objective 2). Centers accredited to treat cancer will be grouped into 6 clusters to define the study sites depending on geographical position. The order in which these groups will have access to the intervention will be randomized. Depending on the stage at which a group is randomized, after a period of usual care of 7, 10, 13, 16, 19, or 22 months, the intervention will run for 22, 19, 16, 13, 10, or 7 months, respectively, in each group. We chose a stepped-wedge design to examine how the effect of the intervention evolves over time, to limit the risk of contamination within a site, and to ensure that the intervention is implemented in a way that maximizes adherence to optimal use, with 1-month training and transition period (see Fig. 2). Further, this type of trial ensures the access to the intervention for all participants. Eligible patients (*N*=750) seeing participating health professionals at these sites will be recruited.

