### Participants

All oncologists practicing in accredited cancer centers will be invited to participate in the stepped-wedge cluster randomized trial. The managers of the RCNs involved in the project will liaise with health professionals in those cancer centers. In both regions 60 cancer licensed centers will be involved in our trial, 44 in Occitanie and 16 in Pays de la Loire. These centers will be classified in 6 randomization groups (clusters), and each cluster will have access to implemented information tools and newly created training resources for practitioners at different times as shown in Fig. 1.

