#### Inclusion criteria for patients

We will include all women over 18 and under 40 years old, treated for a newly diagnosed breast cancer and receiving injectable chemotherapy in one of the participating centers.

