### Sample size and power calculation

We will include all eligible patients over a period of 30 months starting 7 months before randomization of the first cluster and ending 7 months after randomization of the last cluster. This will allow us to reach a total sample of 750 included patients, based on a feasibility assessment of 2/3 of eligible patients recruited in the Occitanie region and 1/3 in the Pays de la Loire region. Assuming a proportion of access to fertility consultation of 23% before the intervention, with 6 clusters of about 120 patients and for an alpha risk of 5%, the smallest detectable effect of the intervention that we will be able to identify with 80% power will be 5.5% points. By knowing the date of the intervention and the date of the PCR, we will be able to identify whether patients were treated as part of usual care or in the intervention phase.

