### Randomization

#### Sequence generation, type of randomization and allocation concealment

We will use an R script from the R software [33] to perform the randomization of the six participating clusters. Randomization will take place at the start of the trial, to determine the order of participation in the intervention of each of the six clusters. Eligible patients of participating health professionals in each cluster will be a priori allocated to the usual care phase before the intervention or to the intervention phase after the intervention. The random allocation sequence will be concealed to health professionals until the beginning of the intervention for their cluster (Fig. 1). The random allocation sequence will likely remain concealed to patients.

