## Data management and statistical analysis

### Data management

The data will be archived on the SYNERGIE secure platform at the University Toulouse III (UT3) and on the EPIDEMIO server at the IUCT Oncopole of Toulouse. Health professional consent forms will also be stored digitally in a dedicated folder on the UT3 secure platform. An anonymous participant ID number will be assigned to each eligible patient of the participating health professionals. A mapping table will be established and managed by the RCN team. This mapping table will be stored digitally in a dedicated folder on a secure platform. Only the RCN project leaders will have access to it.

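### The protocol defines its patients both as all eligible women at the participating centres and as patients of participating professionals only, with 750 attached to each

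*Protocol article*

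**What the plan says.** Three places limit the trial by professional. Trial design attaches N=750 to eligible patients "seeing participating health professionals at these sites will be recruited". The section on sequence generation and allocation concealment says "Eligible patients of participating health professionals in each cluster will be a priori allocated to the usual care phase", and the sentence goes on to cover the intervention phase as well. Data management says "An anonymous participant ID number will be assigned to each eligible patient of the participating health professionals".

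Three places do not. The inclusion criteria open with "We will include all women over 18 and under 40 years old, treated for a newly diagnosed breast cancer" and set participation at the level of the centre: "receiving injectable chemotherapy in one of the participating centers". The exclusion section lists no exclusions. Sample size and power calculation says "We will include all eligible patients over a period of 30 months" and expects this to give 750.

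On the professionals, Participants says "All oncologists practicing in accredited cancer centers will be invited to participate". The randomization section conceals the sequence from them until the intervention begins in their cluster, and Blinding says that they know which phase they are in. The article gives no date by which a professional's participation is settled. It does not say what happens to women whose oncologist declines or joins late.

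**The concern.** The two definitions coincide only if every oncologist takes part. Participation is by invitation, and the objective 2 analysis speaks of training several clinicians at each site, so full participation cannot be assumed.

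What is randomised is the order in which the six clusters cross over. Which oncologists take part within a cluster is not randomised. If the analysed women depend on their oncologist's participation, and participation can be settled after the cluster's turn is known, the phases may differ in whose patients they contain. Oncologists willing to be trained in fertility preservation might already refer more often. That is plausible, but the article gives no data on it. If it were so, the distortion would favour the intervention.

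The milder consequence is that the result describes patients of volunteers, while the inclusion criteria promise all eligible women.

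**Working it through.** **1. The passages side by side**

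| Section | Population |
|---|---|
| Trial design | patients of participating professionals, N=750 |
| Sequence generation and concealment | patients of participating professionals, both phases |
| Data management | ID numbers for patients of participating professionals |
| Inclusion criteria | all women meeting the criteria at a participating centre |
| Exclusion criteria | none |
| Sample size and power calculation | all eligible patients over 30 months, total 750 |

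Both definitions are stated outright, so condensation of a longer protocol does not explain the conflict. The same 750 stands against each.

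**2. Which population the planning figures fit**

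The sample size section assumes a 23% consultation rate before the intervention. The Background reports the same percentage for women under 40 treated with chemotherapy for breast cancer in Occitanie, and does not limit it to patients of volunteering oncologists. That fits the all-eligible definition more naturally. It does not prove what the 750 counts.

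**3. What each reading implies**

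- *All eligible women, both phases.* The oncologist's participation does not affect who is analysed, so no selection arises from it.
- *One list of professionals, fixed before randomisation, both phases.* The same oncologists supply both phases. Selection by participation largely cancels, and the result applies to their patients.
- *Participation settled at or after crossover.* Selection can differ between phases. No section describes this, and no section rules it out.

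**4. Illustration of the third reading (assumed inputs)**

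Let q be the share of eligible women seen by participating oncologists, r1 and r0 the consultation rates among patients of participating and non-participating oncologists without any intervention, and g = r1 − r0. Only the overall 23% comes from the document; q and g are assumed.

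0.23 = q × r1 + (1 − q) × r0, so r1 = 0.23 + (1 − q) × g.

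If usual care held all women and the intervention phase held only participants' patients, the spurious gain would be r1 − 0.23 = (1 − q) × g. For example, q = 0.80 and g = 0.10 give 0.20 × 0.10 = 2.0 points.

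| q | g = 5 points | g = 10 points | g = 15 points | 750 × q |
|---|---|---|---|---|
| 80% | 1.0 | 2.0 | 3.0 | 600 |
| 60% | 2.0 | 4.0 | 6.0 | 450 |
| 50% | 2.5 | 5.0 | 7.5 | 375 |

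With the list fixed and used in both phases, the same expression gives r1 − r1 = 0.

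The last column is the number of women left if 750 counts all eligible women. If it already counts only participants' patients, as Trial design says, nothing is lost.

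For scale, the stated detectable effect is 5.5 points. That figure is only a yardstick here. A simple two-sided comparison of two equal groups totalling 750 (23% usual care, 80% power, alpha 5%) gives 9.1 points, so 5.5 is not reproduced; that is a separate matter.

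**The case against.** The strongest reply is that neither internally consistent reading produces the bias. The randomization section applies its restriction to usual care and intervention alike, and its statement that patients are allocated in advance may imply a list of professionals fixed beforehand. Blinding treats professionals as taking part in both phases. The planned model uses repeated measures by clinician. The ethics and data collection sections describe the same existing records throughout.

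This stands. A reader might infer that usual care takes everyone from the records while the intervention phase takes only volunteers' patients, so that the randomised comparison is already broken. The document describes no such arrangement.

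Three further inferences also go too far:

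- That the sample must fall below 750. Trial design attaches 750 to the restricted group itself.
- That the figures "reported by the 102 of 1161 oncologists who responded to a national survey" predict participation here. They are a response rate to a national survey, not uptake of a trial through the regional networks, and a response rate alone does not show selection.
- That the stored professional consent forms show consent to trial entry. Data management does not say what they are for, and they could belong to the objective 1 focus groups and interviews.

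It can also be said that the timing of professional enrolment belongs in the full protocol. That is fair for the timing. It does not cover two conflicting populations in one article.

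**Conclusion.** The contradiction is certain and should be corrected: three sections restrict by professional, three do not, and 750 is attached to both.

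The selection bias is a possibility that the wording leaves open. It depends on participation being settled after crossover, or on the list differing between phases. If one list is fixed in advance and used throughout, the bias largely disappears and the loss is mainly in whom the result represents. The document does not support saying that the randomised comparison is broken, or that the sample falls short.

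The 1.0 to 7.5 points are conditional on the arrangement in step 4 and on assumed values of 50% to 80% participation and a gap of 5 to 15 points. They show that the matter could be large relative to the 5.5 points sought. They do not estimate a bias in this trial.

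**What to change.** Bring Trial design, the randomization section and Data management into line with the inclusion criteria, exclusion criteria and sample size section:

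- The primary analysis includes every eligible woman treated at the participating centres during the 30 months, except those who object to the use of their data.
- Each woman is classified by her cluster's randomised schedule, whether or not her oncologist took part or was trained.
- The 750 is stated to refer to this population.
- An analysis restricted to participating or trained oncologists is secondary. It uses one list fixed before randomisation and applied to both phases.

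Fixing such a list for the primary analysis would also remove the contradiction, but it would narrow the population and depart from the stated inclusion criteria.

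The cost is mainly wording. Files A and B, which hold age, diagnosis, treatment and oncologist name, and File D, which holds the primary outcome, are queried directly. Including patients of untrained oncologists dilutes the effect somewhat, which is part of what the intervention achieves in routine care. File E (address, number of children, recorded information) is collected from medical records, so these secondary variables may need extra work. The information notice and objection procedure would also have to reach the additional women.
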